#### Sample Size

With 50 individuals randomized to each of the intervention and control groups, this study will have 85% power to detect a difference in mean zMS risk score of 0.6 standard deviation units between groups at follow-up. This is consistent with our previous observational findings from similar cohorts [2] and assumes that the risk score at follow-up in the control group has a mean of 0 and a standard deviation of 1.

#### Definition of Analysis Populations

For the primary trial efficacy analysis, the intention to treat population includes all participants who were randomized. Then, a per-protocol analysis includes all participants from the control group, but only those intervention participants who completed 85% or more of their prescribed exercise sessions. For certain outcomes, sensitivity analyses will be performed with other subsets of participants excluded, e.g. heart rate responses in those on beta-blockers.

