**Methods/Design:**

We aim to recruit 100 participants born between 1931–1939, from the Hertfordshire Cohort Study and randomly assign them to no intervention or to 36 fully supervised one hour sessions on a cycle ergometer, over twelve weeks. Each participant will undergo detailed anthropometric and metabolic assessment pre- and post-intervention, including muscle biopsy, magnetic resonance imaging and spectroscopy, objective measurement of physical activity and sub-maximal fitness testing.

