Many previous studies that have assessed aerobic exercise interventions have yielded physiologically informative data but have inherent methodological limitations in terms of assessing the efficacy of these interventions per se. Some compare different exercise modalities, without including a true "control" group [12]. Where studies have included controls, often only within-group comparisons are reported, rather than considering changes in outcomes in exercisers in the context of changes in the control group [13]: Using the latter approach allows consideration of any measurement effect and would yield a more valid measure of the efficacy of such interventions. Some efficacy analyses have not included study dropouts, or report only on participants who adhered to the intervention in question, rather than conducting an intention-to-treat analysis [14]. Often, attrition rates from exercise interventions are high, thus reducing power [15]. Indeed, inadequate power is frequently cited as an explanation for negative findings in these studies, even where participant retention has been good [16,17].

Some people respond better than others to aerobic exercise interventions in relation to reductions in body fat, improved fitness and changes in metabolic parameters. Several factors underlie this heterogeneity in the response to exercise. In the diabetes prevention trials, older participants gained more benefit from lifestyle interventions than younger ones did [8,18]. Certain genotypes are known to affect the metabolic response to exercise [19]. Individuals with a family history of diabetes derive more benefit from exercise than those without such a history [20]. Metabolic improvements associated with exercise are more pronounced in those with higher metabolic risk [21]. However the factors that influence the response to aerobic exercise in healthy older individuals have not been fully described.

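### The supplementary per-protocol analysis drops poor attenders from the exercise arm but keeps every control, so it is not protected by randomisation and is liable to bias, probably in favour of exercise

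*Protocol article*

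**What the plan says.** All places are in the protocol article.

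- **Definition of Analysis Populations** puts intention to treat first: "For the primary trial efficacy analysis, the intention to treat population includes all participants who were randomized". It then defines a per-protocol analysis that "includes all participants from the control group, but only those intervention participants who completed 85% or more of their prescribed exercise sessions".
- **Abstract, Methods/Design** gives the prescription as "36 fully supervised one hour sessions on a cycle ergometer, over twelve weeks" and the control condition as no intervention. Controls therefore have no attendance on which they could be filtered.
- **Analysis of the primary outcome** specifies linear regression of follow-up zMS with baseline zMS as the covariate.
- **Exploratory Analyses** allows poorly balanced covariates to be considered as confounders in later analyses.
- **Missing data** leaves out anyone without a follow-up value for the outcome concerned.
- **Background** lists, among the weaknesses of earlier trials, that some "report only on participants who adhered to the intervention in question, rather than conducting an intention-to-treat analysis".

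**The concern.** Attendance is observed after randomisation and only in one arm. Exercisers who reach 85% may differ in health or motivation from those who do not. The controls who would have attended equally well cannot be identified, so they stay mixed with those who would not. The difference between the two groups then combines any effect of exercise with the prognostic difference between good attenders and everyone.

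The cut is not remote. At three sessions a week, two missed weeks leave 30 of 36 sessions (83.3%), which excludes the participant unless sessions are made up. An exerciser who is ill for a fortnight can drop out of the set, while a control with the same illness remains. Such an event comes after baseline, so the baseline score cannot be relied on to account for it.

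What is at stake is interpretation. The trial is described as explanatory, and a per-protocol result is easily taken as the effect in people who actually exercised. This analysis does not estimate that without further assumptions.

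**Working it through.** **1. The plan's own figure.** The inputs from Sample Size are 50 per arm, a difference of 0.6 and SD 1. Alpha is not stated there; 0.05 two-sided is assumed.

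- SE = √(2/50) = 0.20, and 0.6/0.20 = 3.0.
- Power = Φ(3.0 − 1.96) = Φ(1.04) = 0.851 (0.844 with the noncentral t).

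The stated 85% is reproduced, so the sample size is not in question.

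**2. The cut.** 0.85 × 36 = 30.6, so at least 31 sessions are needed (31/36 = 86.1%).

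**3. Model for the bias (assumed inputs).** Take no true effect, 50 per arm and a baseline to follow-up correlation of 0.7. Follow-up zMS is 0.7 × baseline + √(1 − 0.49) × e = 0.7 × baseline + 0.714e, where e is the part that baseline does not explain. A latent attendance variable is correlated with baseline, with e, or with both, so that lower risk goes with better attendance. The top share q of the exercise arm is kept, all controls are kept, and the planned baseline-adjusted regression is fitted.

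If attendance is correlated r with e only, the expected bias is −r × [φ(z)/q] × 0.714, where z is the (1 − q) normal quantile.

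- q = 0.7, r = 0.3: φ(−0.524)/0.7 = 0.348/0.7 = 0.497, and 0.3 × 0.497 × 0.714 = 0.106.
- q = 0.9, r = 0.15: φ(−1.282)/0.9 = 0.1755/0.9 = 0.195, and 0.15 × 0.195 × 0.714 = 0.021.

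**4. Simulation of the same model.** There were 4,000 runs per cell. Entries are the baseline-adjusted difference in zMS SD units (negative favours exercise), with two-sided type I error in brackets.

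| Attendance related to | 90% kept | 80% kept | 70% kept |
|---|---|---|---|
| Nothing relevant to outcome | −0.001 (0.046) | −0.003 (0.054) | −0.004 (0.048) |
| Baseline only, 0.3 | 0.000 (0.049) | −0.002 (0.053) | −0.005 (0.051) |
| Baseline 0.3, residual 0.15 | −0.022 (0.049) | −0.037 (0.053) | −0.054 (0.066) |
| Baseline 0.3, residual 0.3 | −0.045 (0.063) | −0.079 (0.076) | −0.110 (0.103) |
| Residual only, 0.3 | −0.043 (0.060) | −0.072 (0.077) | −0.108 (0.102) |
| Baseline 0.3, residual −0.15 (reversed) | +0.018 (0.045) | +0.036 (0.058) | +0.052 (0.058) |

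In the baseline-only row, the unadjusted differences are −0.039, −0.077 and −0.108. Baseline adjustment removes nearly all of that selection. It does not remove selection on the residual. The Monte Carlo error of a rejection rate near 0.05 is √(0.05 × 0.95/4000) = 0.003.

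**5. Scale.** Against the 0.6 SD target, 0.022/0.6 = 4% and 0.110/0.6 = 18%.

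**The case against.** The strongest reply is that this analysis is supplementary. Intention to treat is named as the population for the primary efficacy analysis, so a reader who infers that the main conclusion is at risk goes further than the text allows. That part of the reply stands in full.

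A reader might also infer that the plan commits the fault it criticises in the Background. It does not. That criticism is of reporting adherers in place of intention to treat, and this trial plans both.

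Nor do the documents show that the result is biased towards exercise. They give no attendance rate, no predictors of attendance and no reasons for missed sessions. That direction is the usual expectation, but other patterns give no bias or the opposite sign.

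A larger figure is also tempting. The gap between adherers and the whole arm is (1 − p)d, where p is the share adherent and d the prognostic gap between adherers and non-adherers. With p = 0.7 and d = 0.5 SD this is 0.3 × 0.5 = 0.15 SD, a quarter of the target. Both inputs are assumed, and the figure applies to the planned model only if d is what remains after baseline adjustment. If d = 0.5 is measured in residual SDs, the result on the zMS scale is 0.15 × 0.714 = 0.107, within the range above.

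Finally, a label such as supportive may stand in a fuller plan that is not shown, and its absence from the article is not the point. The rule for forming the set is stated, and a label would not change what that set compares. Considering unbalanced covariates as confounders helps only for what was measured.

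**Conclusion.** The concern holds as a weakness of the supplementary adherence analysis. The one-sided exclusion is explicit, and nothing elsewhere in the article restores the randomised comparison. The likely bias is modest: about 0.02 to 0.11 SD in favour of exercise after baseline adjustment, with type I error up to about 0.06, 0.08 and 0.10 at 90, 80 and 70% retained.

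Those figures rest on assumed correlations of 0.15 to 0.3 with the follow-up residual, an assumed baseline to follow-up correlation of 0.7, and assumed retention. None of these comes from the documents. Confidence is high that the contrast is unprotected, lower on the direction, and limited on the size. It is a change worth making, not a threat to the trial's main result.

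**What to change.** Make the adherence analysis a complier-average causal effect. Use two-stage least squares with randomised arm as the instrument for attendance (sessions attended as a share of 36). Adjust for baseline zMS and the minimisation factors: birth weight, percentage body fat, gender and whether a biopsy was done. Include all randomised participants with follow-up data, since the missing-data rule excludes the rest. Controls are offered no sessions, so non-adherence is one-sided. The estimate is in essence the intention-to-treat difference divided by mean attendance in the exercise arm, and so it keeps the randomised comparison. Label any 85% subset comparison descriptive.

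The change is to analysis wording only, because the 85% rule already requires attendance records. The costs are:

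- **A wider interval**, by roughly 1/mean attendance. If mean attendance were 0.8 (an assumption), that is 1/0.8 = 1.25 times.
- **Two assumptions to state**: that assignment acts only through sessions attended, and that the effect is proportional to their number. The second is approximate, because the Exercise Intervention section raises intensity across the twelve weeks, so early and late sessions are not equivalent.
- **No new evidence against the null**. The test of no effect is essentially the intention-to-treat test; what is gained is an estimate on the scale of full attendance.
- **Dependence on follow-up**. If those lost to follow-up are mainly low attenders, this estimate shares that weakness with the primary analysis.

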#### Analysis of the primary outcome

The primary analysis compares the composite metabolic risk score at follow-up, adjusted for baseline, between the intervention and control groups. A linear regression model will be used, with follow-up risk score as the outcome and baseline risk score as a covariate.

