## Methods/Design

### Study design

This is a single centre, explanatory randomized controlled trial of the efficacy of a fully supervised twelve-week aerobic exercise intervention to reduce overall metabolic risk in healthy older people. Participants are randomized to exercise or control groups following minimisation according to birth weight, percentage body fat, gender and whether or not a muscle biopsy has been performed. The duration of follow-up is 12 weeks from study entry.

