#### Missing data

Individuals with a missing value for an outcome variable at follow-up will be excluded from the analysis of that variable. Where the baseline value of a particular outcome is missing, the missing indicator method [67] will be used in sensitivity analyses.

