#### Exploratory Analyses

In exploratory analyses, the linear regression model described above will be extended to include an interaction between birth weight and randomized group, to assess whether the effect of the intervention differs according to birth weight. Although this is a randomized trial, there may be some covariates which are not sufficiently well balanced between the exercise and control groups, and where this occurs, these will be considered as potential confounders in subsequent analyses.

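### The primary model leaves out the four minimisation factors, so its standard error may be somewhat too large and the test mildly conservative

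*Protocol article*

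**What the plan says.** Under Study design, the Protocol article says that participants are allocated "following minimisation according to birth weight, percentage body fat, gender and whether or not a muscle biopsy has been performed". Under Analysis of the primary outcome, it fixes the model: "A linear regression model will be used, with follow-up risk score as the outcome and baseline risk score as a covariate". No minimisation factor appears there. Analysis of the secondary outcomes carries the same method over to all other outcomes.

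Two further statements bear on adjustment, both under Exploratory Analyses. One extends the model with an interaction between birth weight and randomised group. The other notes that "there may be some covariates which are not sufficiently well balanced between the exercise and control groups, and where this occurs", those covariates will be considered as potential confounders in later analyses.

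The only precision figure is under Sample Size: "this study will have 85% power to detect a difference in mean zMS risk score of 0.6 standard deviation units between groups at follow-up". The article states no standard error.

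**The concern.** The stated analysis does not reflect the stated allocation. Minimisation removes most of the chance imbalance on its factors, so the treatment estimate varies less from trial to trial than it would under simple randomisation. A model that omits the factors does not know this. It leaves whatever they explain in the residual and computes a standard error as if they could still be imbalanced. The confidence interval is then wider than it need be, and the test rejects a true null less often than its nominal level.

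At stake is efficiency in a trial of 100 people, for the primary outcome and for a long list of secondary outcomes. The imbalance rule under Exploratory Analyses does not make up for the omission. It would rarely pick the minimisation factors, because minimisation keeps them balanced, and it lets the covariate set of those later estimates depend on the data.

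**Working it through.** **Inputs from the article**
- 50 per arm (Sample Size).
- Difference 0.6 and SD 1, both on the scale of the follow-up score. Sample Size "assumes that the risk score at follow-up in the control group has a mean of 0 and a standard deviation of 1".
- Minimisation factors from Study design; model covariates from Analysis of the primary outcome.

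**Assumptions (not in the article)**
- Alpha 0.05 two-sided. This reproduces the stated power; one-sided 0.05 would give 91.2% and two-sided 0.01 would give 66.4%.
- Correlation ρ between baseline and follow-up score: 0.5 to 0.7, with 0 as the planning basis.
- Partial R² of the four factors given baseline: 0 to 0.20.
- For simulation: four binary factors, and minimisation with a biased coin of 0.8.
- All 100 participants analysed.

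**Step 1. Reproduce the stated power.** SE = 1 × √(2/50) = 0.200. Then 0.6/0.200 = 3.00, 3.00 − 1.96 = 1.04, and Φ(1.04) = 85.1%. The noncentral t gives 84.4%. The stated 85% is reproduced, with no credit for baseline or any other covariate.

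**Step 2. Power by formula.** Baseline adjustment gives residual SD √(1 − ρ²): 0.866 at ρ 0.5 (SE 0.866 × 0.200 = 0.173) and 0.714 at ρ 0.7 (SE 0.143). Adding the factors multiplies the SE by √(1 − R²): 0.975 at R² 0.05, 0.949 at 0.10, 0.894 at 0.20. Power (%), noncentral t:

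| ρ | Difference (SD) | Baseline only | + factors, R² 0.05 | R² 0.10 | R² 0.20 |
|---|---|---|---|---|---|
| 0 | 0.6 | 84.4 | 86.1 | 87.9 | 91.3 |
| 0.5 | 0.6 | 92.9 | 94.0 | 95.1 | 96.9 |
| 0.7 | 0.6 | 98.6 | 98.9 | 99.2 | 99.6 |
| 0.5 | 0.4 | 62.8 | 65.0 | 67.3 | 72.4 |

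At R² 0, adding the factors changes power by less than 0.1 point. At 0.6 SD the gain at ρ 0.5 is 1.1, 2.2 and 4.0 points for R² 0.05, 0.10 and 0.20. At ρ 0.7 it is 0.3, 0.6 and 1.0. At 0.4 SD and ρ 0.5 it is 2.2, 4.5 and 9.6.

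**Step 3. Model SE against true sampling variation.** 4,000 simulated trials of 100 per setting, allocated by minimisation:

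| ρ | R² | Mean model SE, baseline only | True SD of estimate | Ratio | Type I error, baseline only | Type I error, factors added |
|---|---|---|---|---|---|---|
| 0.5 | 0 | 0.1734 | 0.1726 | 1.00 | 4.8% | 5.0% |
| 0.5 | 0.10 | 0.1740 | 0.1675 | 1.04 | 4.1% | 5.2% |
| 0.5 | 0.20 | 0.1739 | 0.1559 | 1.12 | 2.9% | 4.8% |
| 0.7 | 0.10 | 0.1431 | 0.1358 | 1.05 | 3.9% | 5.0% |
| 0.7 | 0.20 | 0.1432 | 0.1294 | 1.11 | 3.0% | 4.9% |

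Simulation error on a 5% rate is √(0.05 × 0.95/4000) = 0.34 points. With the factors in the model, type I error stays between 4.8% and 5.3% in every setting run.

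Simulated power gains at 0.6 SD are smaller than the formula gives: 0.6 to 2.6 points at ρ 0.5 and 0.2 to 0.6 at ρ 0.7, for R² 0.05 to 0.20. Under minimisation the baseline-only estimate already varies less than its SE suggests, so the formula understates baseline-only power.

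**The case against.** The strongest reply is that the loss may be nil. The article gives no partial R², and there are reasons to expect a low one for the primary outcome. The score's components are standardised within sex, waist circumference is one of them, birth weight is a fixed trait whose influence should largely show in the baseline score, biopsy status marks a procedure, and follow-up is only 12 weeks. All of this stands and limits the size. It is weaker for secondary outcomes such as fitness or fat-free mass, for which no sex-specific standardisation is described, although their own baseline values also absorb part of the effect.

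A fuller analysis plan may also name the factors. That is possible, but the article does not leave the covariate set open; it states one.

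Four stronger readings are tempting, and the documents do not support them.
- A reader might infer that the 85% power is wrong or that substantial power is lost. The 85% takes no credit for covariates, and baseline adjustment alone gives 92.9% at ρ 0.5 before any dropout.
- A reader might infer that covariates enter the primary model when imbalance is seen. That rule sits under Exploratory Analyses and applies to later analyses; the primary estimate and its SE are untouched.
- A reader might infer that imbalance is the only route to further adjustment. The birth-weight interaction model is also prespecified.
- A reader might infer a risk of false positives. The error runs the other way.

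**Conclusion.** The mismatch is real and its consequence modest. The primary model, and through it the secondary analyses, omits all four minimisation factors. If they are prognostic beyond baseline, the model-based SE is too large: at ρ 0.5, by about 4% at partial R² 0.10 and about 12% at 0.20, with type I error of about 4.1% and 2.9%. At R² 0 nothing changes.

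At the planned 0.6 SD, adjusting gains about 0 to 2 power points for R² up to 0.10 and up to about 4 at 0.20, for ρ 0.5 to 0.7. On the planning SD of 1 with no baseline credit, the formula gain at R² 0.20 would be 91.3 − 84.4 = 6.9 points, but the planned analysis does adjust for baseline. Smaller true effects gain more.

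These sizes rest on the assumed alpha, ρ, R², binary factors and biased coin. They also assume complete follow-up, whereas the Sample Size section makes no allowance for dropout and under Missing data "Individuals with a missing value for an outcome variable at follow-up will be excluded from the analysis of that variable". This is an efficiency and consistency point. It does not threaten validity.

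**What to change.** Under Analysis of the primary outcome, and so for the secondary outcomes, add birth weight and percentage body fat as continuous terms, plus gender and biopsy status, as prespecified covariates beside the baseline value. The simulation used binary factors, so the continuous form was not itself tested; continuous terms avoid discarding information through cut-points.

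The cost is one sentence and four degrees of freedom: with 100 analysed, residual degrees of freedom fall from 100 − 3 = 97 to 93. All four variables must be known before allocation, so no new data are needed.

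Separately, and as a minor point, replace the imbalance trigger under Exploratory Analyses with a covariate list fixed in advance by expected prognostic value. This does not touch the primary analysis.

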#### Analysis of the secondary outcomes

The method used to analyse the primary outcome will also be used to analyse the secondary outcomes. For outcomes which do not have a normal distribution, a log transformation will be applied.

#### Missing data

Individuals with a missing value for an outcome variable at follow-up will be excluded from the analysis of that variable. Where the baseline value of a particular outcome is missing, the missing indicator method [67] will be used in sensitivity analyses.

#### Exploratory Analyses

In exploratory analyses, the linear regression model described above will be extended to include an interaction between birth weight and randomized group, to assess whether the effect of the intervention differs according to birth weight. Although this is a randomized trial, there may be some covariates which are not sufficiently well balanced between the exercise and control groups, and where this occurs, these will be considered as potential confounders in subsequent analyses.

## Discussion

Compelling observational data suggest that older people who engage in exercise are fitter and healthier and have lower cardiovascular risk, but higher level evidence that exercise interventions are beneficial in this group is currently lacking. This study will assess the efficacy of such an intervention to improve composite metabolic risk and other endpoints such as glucose tolerance status and insulin sensitivity. The feasibility and safety of a fully supervised, gym-based aerobic exercise programme will also be determined. The extent to which supervised exercise influences habitual physical activity levels will also be explored, as previous work has suggested that compensatory reductions in non-exercise physical activity in older people might negate any benefits [68]. We have not included a dietary modification component to this lifestyle intervention, as to do so may introduce uncertainty as to the mechanisms underlying any observed metabolic improvements. Furthermore, there is some evidence that exercise alone is superior to combined exercise and dietary interventions [69], although other studies suggest combined interventions are best [70]. Observational findings that low birth weight increases subsequent metabolic risk only in adults who are less fit suggests that exercise may have greater benefits in low birth weight individuals [3]. This study is well placed to elucidate any interactions between birth weight and the metabolic response to aerobic exercise, given the relatively large number of participants and the extensive physiological characterization that is involved. This will also allow assessment of other potential determinants of exercise responses, such as diabetes family history. The study will provide valuable opportunities to validate new techniques for measuring body composition and physical activity energy expenditure, both of which are critically important epidemiological outcomes. In addition to a trial efficacy analysis, subsequent cohort analyses will allow the exploration of the effects of birth weight on responses to changes in fitness and body composition. The findings will consolidate our understanding of the putative benefits of exercise in older people, and the mechanisms through which they occur.

